### Evaluation frameworks

Two complementing theoretical frameworks will be used to guide the evaluation: the Reach, Evaluation, Adoption, Implementation and Maintenance (RE-AIM) framework [25] and the Practical Robust Implementation and Sustainability Model (PRISM) framework [26], which is an extension of the RE-AIM framework. Specifically, to conceptualize the evaluation outcomes (i.e., service *Reach* and *Effectiveness*, including consideration of *Adoption* characteristics, *Implementation* process and the potential for long-term *Maintenance*) we will be guided by the RE-AIM framework. The PRISM framework will be used to systematically identify and assess multi-level contextual factors hypothesized to affect the RE-AIM outcomes. Specifically, this evaluation will assess how the perspectives of stakeholders including the service providers, the characteristics of recipients, the implementation and sustainability infrastructure of the organization, and the external environment, influence the evaluation outcomes. Furthermore, this evaluation was designed and will be delivered under the governance of a project steering group comprising academic, clinical and state department organization representatives and peer researchers with lived experience. Figure 1 provides an overview of the project design, illustrating the integration of the RE-AIM and PRISM frameworks.

**Fig. 1 Fig1:**
[figure not shown]
Overview of the project design illustrating the integration of RE-AIM and PRISM

### Study design

A mixed methods evaluation will be conducted over a five-year period. It will employ a type I hybrid effectiveness-implementation design [27], which focuses primarily on determining the effectiveness of an intervention, while exploring the context for implementation.

The RE-AIM and PRISM frameworks will inform all aspects of this evaluation, including development of the program logic map (see supplementary material 1), evaluation outcomes, selection of quantitative measures, and semi-structured interview guides. Table 1 provides a detailed overview of the study design, including evaluation domains and corresponding research questions, outcomes, operational definitions, measures, and data sources. This also provides a focal point for evaluation planning and supports the mapping of evaluation methods and associated data sources to program logic elements.

**Table 1 Tab1:** Overview of study design, including domains of interest

**RE-AIM domain**	**Research Questions**	**Outcomes**	**Operationalization**	**Measures**	**Data Sources**									
					**Users**				**Providers**			**Systems**		
					**YP**		**Family**							
					Survey	Interview	Survey	Interview	Survey	Interview/ workshop	EOT form	ROM	Hospital	SHMS
Reach	Is the service reaching young people presenting with self-harm or suicidal ideation to ED in the catchment area? Who participates in the service and how do they participate over time?	*Participation (YP/Family)*	Proportions of service users presenting to ED who were eligible and who participated in HOPE aftercare	Routinely collected variables/data									X	
		*Engagement (YP/Family)*	Proportions of service users moving through the service including the referral, intake, retention and discharge points	Routinely collected variables/data									X	
		*Participant characteristics* *(YP/Family)*	Characteristics of service users (e.g., age, gender, location, priority group, mental health diagnosis, comorbidities, hospital presentations)	Routinely collected variables/data									X	
	What barriers/facilitators to participation exist?	*Barriers/Facilitators*	Identification of barriers and facilitators	Open-ended questions		X		X		X				
Adoption	How and when are ED staff referring young people to the service?	*Participation (Staff)*	Characteristics of the referral pathways	Routinely collected variables/data							X		X	
	What are the characteristics of the participating service system and health providers?	*Engagement (Staff)*	Characteristics of providers (e.g., age, gender, years of service, professional background, roles)	Demographic variables					X					
		*Service setting**characteristics*	Characteristics of the service setting (e.g., organizational climate and culture, service resources, leadership capacity, staff integration)	CFIR–IS ILS PSI					X					
		*Provider characteristics*	Characteristics of providers’ training, knowledge, self-efficacy and attitudes/perceptions about suicide	Purpose-developed items based on existing measures. ASP scale					X					
	What barriers/ facilitators exist, and how do they affect the program access, engagement and efficacy?	*Barriers/Facilitators*	Identification of barriers and facilitators	Open-ended questions		X		X		X				
Implementation	What are the contextual factors (i.e., organizational, system and individual) impacting implementation?	*Moderators*	Descriptors of changes or modifications to the intervention							X	X			
	How satisfied are young people/family members with the service?	*Satisfaction*	User satisfaction rates	Routinely collected data Purpose-developed questions		X		X	X	X		X		
	What level of delivery is the program achieving? What are the components getting delivered, are there any adaptations?	*Treatment adherence*	Descriptors of treatment components and methods of delivery	Purpose-developed questions							X			
	Is the service acceptable, appropriate and feasible from the perspectives of young people, support persons and providers?	*Acceptability*	Proportions of users and providers ratings	AAF Open-ended questions	X	X	X	X	X	X				
Effectiveness	For young people, does engaging with the service lead to: - Reduced self-reported self-harm, suicide ideation and attempts - Reduced re-presentations to ED - Improved mental health related to depressive symptoms and psychological distress? - Increased treatment engagement, social/vocational functioning and quality of life?	*Effectiveness*	Significant reduction from baseline to posttreatment on frequency and severity of suicidal ideations (primary outcome), and frequency and severity of self-harm and suicide attempts	SIDAS YRBS Self-harm (purpose-developed questions)	X		X							
			Significant reduction in hospital (re-)presentation trends to ED since the implementation of HOPE aftercare	Hospital (re)presentation rates (Surveillance data)										X
		*Improved mental health*	Significant improvement on mental health indicators	PHQ–9 GAD–7 K10 PSS	X		X							
		*Better functioning*	Treatment completion and dropout rates Significant improvement in functioning and quality of life	CHU–9D	X	X					X		X	
	Is the service safe?	*Safety*	Significant deterioration of symptoms Occurrence of serious adverse events	SIDAS, suicide attempt or hospital admission	X								X	
	Is the service acceptable, appropriate and feasible from the perspectives of young people, support persons and providers?	*Acceptability*	Proportion of service users and providers	AAF	X		X				X			
	Is the service cost-effective?	*Cost-effectiveness*	Program costs and costs of additional healthcare services (i.e., hospital presentations and psychological treatment) relative to quality of adjusted life years.	Hospital re-presentation RUQ CHU–9D	X								X	X
Maintenance	What are the long-term effects of the service on individual outcomes?	*Effectiveness (at follow-up)*	Significant further reduction or maintenance of symptoms at follow-up on measures of intensity and severity of suicidal ideations (primary outcome) and suicide attempt, self-harm, and mental health indicators and quality of life	SIDAS YRBS Self-harm (purpose developed questions) PHQ–9 GAD–7 K10 CHU–9D	X								X	X
	What are the likely impacts of the service when delivered at scale and within the current service eco-system?	*Scalability*	Computer-based system dynamics model											X

*EOT form *routinely collected end-of-treatment form, *ROM *Routine Outcome Measure, *Hospital* patient’s electronic medical records, *SHMS *Self-Harm Monitoring System for Victoria, *CFIR–IS *Consolidated Framework for Implementation Research Inner Setting measures [28], *ILS *Implementation Leadership Scale [29], *PSI *Program Sustainability Index [30], *ASP *Attitudes to Suicide Prevention Scale [31], *AAF *Acceptability, Appropriateness and Feasibility measures [32], *SIDAS *Suicidal Ideation Attributes Scale [33], *YRBS *United States Centers for Disease Control and Prevention’s National Youth Risk Behavior Survey [34], *PHQ–9 *Patient Health Questionnaire–9 [35], *GAD–7 *Generalized Anxiety Disorder Scale [36], *K10 *Kessler Psychological Distress Scale [37], *CHU–9D *Child Health Utility–9D [38, 39], *RUQ * Resource Use Questionnaire [40]

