**Discussion:**

Findings from this evaluation will determine the effectiveness, including cost-effectiveness, of the HOPE aftercare service and describe the implementation context. They will inform the future development and sustainability of this and other similar services across Australia and internationally.

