## Intervention

The Orygen HOPE aftercare is an evidence-informed, psychosocial program that provides intensive, person-centered, multi-disciplinary coordinated support which is tailored to the unique needs and circumstances of the individual young person using Relational Clinical Care (RCC) (see Table 2).

**Table 2 Tab2:** HOPE aftercare core RCC components

The core components of RCC		
Collaborative formulation, diagnosis, and psychoeducation		
Establishing and attending to the therapeutic relationship with young person and carers to enhance engagement and reduce barriers to treatment		
Family, carer, and system inclusive practice		
Young person and carer lived-experience peer support		
Brief intervention and time-limited episodic care		
Focus on the episode of care with a shared understanding of endings and supported transitions		
Collaborative care planning, including:		
a) Identification of co-occurring difficulties contributing to the acute presentation b) Goal setting c) Shared decision making and formulated treatment planning.		
Consistency and containment within the HOPE team via supervision and reflective clinical discussions.		

Young people referred to the Orygen HOPE aftercare are contacted within 24-hours of hospital/ED discharge; in-person assessment is arranged within 72-hours of the initial referral, and treatment is provided for up to three months. The RCC model positions the young person as the leader of the care team, and the multidisciplinary team delivers holistic support across psychological, family, psychosocial, and physical domains. The main feature of the HOPE service is collaborative work with the young person’s support system (family/carers, educational/vocational, healthcare, and community support providers) to understand, respond to and meet the wellbeing needs of the young person.

Young people referred to the Orygen HOPE aftercare will receive an assessment and treatment under the care of the Orygen HOPE multidisciplinary team. This consists of a consultant psychiatrist, psychiatric registrar, and allied health staff (clinical psychologist, psychologists, social workers, occupational therapists) providing clinical services. Youth peer workers and family peer workers are employed to provide additional support services. Orygen HOPE aftercare is governed directly by a lead consultant psychiatrist and team coordinator and sits within the broader governance structures of Orygen clinical specialist programs.

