### Participants

#### Young people and carers

All young people (aged 12–25) who receive care from the Orygen HOPE aftercare will be invited to participate in the evaluation. Recruitment of participants will be facilitated by the Orygen HOPE clinical team. Following admission to Orygen HOPE aftercare, Orygen HOPE clients are presented at the clinical team meetings for discussion and allocation. A research team member will attend these meetings to be informed about the admission of new clients and to determine when to approach potential participants. Family members, support persons, and carers will also be invited to participate. To be eligible for the service, young people must meet the following criteria:

▪ Age between 12 and 25 years.▪ Presented to EDs within western and north–western metropolitan Melbourne following suicide attempt, or an episode of severe self-harm and/or significant levels of suicidal ideation.

Young people will be excluded from the service and referred to other appropriate services (e.g., other Orygen clinical services), if they present with any of the following criteria:

▪ Currently engaged in case management. ▪ Require acute care (will be initially managed by Orygen Acute).▪ Under a compulsory treatment order.▪ Present with psychotic symptoms or symptoms of hypomania or mania.▪ Have a complexity of mental health and psychosocial needs indicating a need for longer term case management or intensive care.

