### Data collection

To facilitate the evaluation, a range of data collection strategies and sources will be used, including electronic hospital records, self-report data, and surveillance and monitoring data (see Table 1).

Epidemiological data on rates of self-harm and suicidal ideation presentations across the catchment area will be obtained from routinely collected data extracted from electronic patient medical records. These data will be collected every six months throughout the life of the project and will provide information relevant to patients’ demographic characteristics, hospital presentations, referral sources, clinical descriptors, and assessments.

Patient-reported data will include data collected directly from young people and carers/parents/family members. Young people and family members will be recruited and consented to participation by the research team at the beginning of the young person’s treatment episode. Young people will provide quantitative survey responses at Time 1 (Baseline: at intake into treatment), Time 2 (Posttreatment: at discharge from treatment), and Time 3 (Follow-up: 3-months post–discharge from treatment). Family members/carers will provide quantitative survey responses at Time 1 and Time 2. Semi-structured interviews will be undertaken following completion of treatment with a select group of young people and family members/carers (*N* = 6–12 participants in each group). Interviews will be conducted in person or via video conference. The interviews will be conducted in Year 2 and Year 4 of this evaluation, allowing the service an opportunity to mature.

Service provider reported data will be collected via self-report surveys, individual semi-structured interviews, and group discussion via workshops, which will be undertaken annually. Specifically, surveys and interviews will be used to assess barriers and facilitators of the implementation across the five years. Workshops will be scheduled annually with the whole group of service providers and facilitated by the research team. The workshop discussion allows for appraisal of service strengths and weaknesses, and identification/prioritization of areas that need improvement. Using this methodology, providers identify the changes individually (via surveys) and then discuss responses in a participatory workshop to identify what needs to be improved to sustain the service.

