#### Primary outcome

*Suicidal ideation* will be measured using the Suicidal Ideation Attributes Scale (SIDAS; [29]). The SIDAS consists of five items (rated 0–10) each targeting an attribute of suicidal thoughts over the past month: frequency, controllability, closeness to attempt, level of distress associated with the thoughts, and impact on daily functioning. The SIDAS has demonstrated strong internal consistency and good convergent validity in a large online sample of Australian adults, including young people aged 18 and above [29].

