#### Secondary outcomes

*Suicide attempts* will be assessed using four items from the United States Centers for Disease Control and Prevention’s National Youth Risk Behavior Survey (YRBS; [30]) assessing frequency and severity of suicide attempts over the past month. The YRBS displays appropriate psychometric properties for use with young people aged 13 to 18, including test–retest reliability [30].

*Self-harm* will be assessed using purpose-developed questions assessing type and frequency of self-harm events in the past month (e.g., “Have you ever engaged in an act of self-harm (with or without suicidal intent)? If yes, have you engaged in this behavior in the last month?”).

*Depressive symptoms* will be assessed using the 9-item Patient Health Questionnaire–9 (PHQ–9; [31]). The PHQ–9 focuses on severity of symptoms experienced over the past two weeks, with items rated on a 4-point Likert scale. It has established reliability and validity in acute and primary care [31], including young people [32, 33].

*Anxiety symptoms* will be assessed using the 7-item Generalized Anxiety Disorder Scale (GAD–7; [34]). The GAD–7 focuses on the frequency of symptoms experienced over the past two weeks, with items rated on a 4-point Likert scale. The GAD–7 has established reliability and validity in acute and primary care [31], including young people [35, 36].

*Psychological distress* will be assessed using the 10-item Kessler Psychological Distress Scale (K10; [37]). The K10 assesses generalized psychological distress experienced over the preceding 30 days. Items are rated on a 5-point Likert scale. The K10 has established reliability and validity across a variety of samples [37], including the Australian general population [38] and Australian adolescents [39].

*Mental health resource use* will be assessed using items adapted from the Young Mind Matters Service Use Questionnaire [40], referred to as the Resource Use Questionnaire (RUQ) for the purposes of the proposed study. These items assess relevant resource use (e.g., mental health services, ED attendance).

*Quality of life* will be assessed using the Child Health Utility–9D (CHU-9D) measure [41, 42]. The CHU–9D is a generic preference-based instrument designed to assess quality of life and facilitate economic evaluation of preventative and healthcare treatment programs aimed at young people. The CHU–9D has demonstrated practicality, face, and construct validity within a sample of Australian adolescents [43].

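### Table 1 counts a significant uncontrolled fall from a crisis-time baseline as effectiveness, and natural recovery can meet that rule without any service effect

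*Protocol article*

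**What the plan says.** The Effectiveness row of Table 1 (Study design) asks a causal question, whether engaging with the service leads to less ideation, self-harm and attempts. It answers it with this criterion: "Significant reduction from baseline to posttreatment on frequency and severity of suicidal ideations (primary outcome), and frequency and severity of self-harm and suicide attempts". The Discussion part of the Abstract draws the matching conclusion: "Findings from this evaluation will determine the effectiveness, including cost-effectiveness, of the HOPE aftercare service".

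The Data analysis plan examines change over three time points in people who received the service, using a linear mixed effects model for continuous outcomes and GEE for binary ones. It names no comparison group for the survey measures. The historical control uses the Self-Harm Monitoring System for Victoria, compares 2012–2021 with 2022–2026, and concerns ED presentation rates and time to re-presentation.

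The timing is as follows.
- Entry (Participants): ED presentation "following suicide attempt, or an episode of severe self-harm and/or significant levels of suicidal ideation".
- Start of care (Intervention): "contacted within 24-hours of hospital/ED discharge; in-person assessment is arranged within 72-hours of the initial referral, and treatment is provided for up to three months".
- Surveys (Data collection): "Time 1 (Baseline: at intake into treatment), Time 2 (Posttreatment: at discharge from treatment"), with a third survey three months after discharge.
- Recall: the SIDAS has five items, "each targeting an attribute of suicidal thoughts over the past month". The YRBS items are described as "assessing frequency and severity of suicide attempts over the past month". The purpose-developed self-harm questions use the same one-month window.

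**The concern.** People enter the study because of a crisis, and the baseline is measured close enough to it that a one-month look-back will normally include it. After a full-length episode of about three months, the one-month window at discharge no longer does. Scores would be expected to move down to some degree even if the service did nothing. A significance test of within-person change cannot separate that movement from a service effect, and no choice of mixed model or GEE can do so without comparator data.

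For self-harm and attempts the problem is partly built in. A participant who entered after such an event and is surveyed within a month of it is positive at baseline on the binary past-month indicator by selection, so for that participant the indicator cannot rise.

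At stake is the primary conclusion. The rule could label an inert service effective. The Economic evaluation section says user-survey data will inform that work, and the system-dynamics model draws on project data, so an unattributable change might also be carried forward.

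**Working it through.** **1. The plan's own figure.** Sample size and power gives N = 184 for a medium effect, r = 0.5 and 30% drop-out. Alpha, sidedness and power are not stated; I assume 5% two-sided, 80% power and d = 0.5.
- SD of change = SD x sqrt(2(1 − r)) = SD x sqrt(1) = 1 SD.
- Two-group t-test on change: 64 per group; 64/0.7 = 91.4, so 92; 2 x 92 = **184**. This matches. (A two-group ANCOVA at 90% power also gives 64 per group and 184.)
- Single-group paired t-test, the design described: 34 completers; 34/0.7 = 48.6, so **49**. This does not match.
- Single-group paired t-test at d = 0.25: 128 completers; 128/0.7 = 182.9, so 183. This is close, but 0.25 is not normally called medium.

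Used for a single-group change, 184 therefore gives a very sensitive test.

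**2. Smallest fall that meets the rule.** Completers: 184 x 0.7 = 128.8, taken as 128. Critical mean fall = t(0.975, 127)/sqrt(128) = **0.175 SD**.

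**3. Chance that a zero-effect service meets the rule.** Let δ be the natural fall in SD units. Then P = 1 − F(t(0.975, 127)), where F is the noncentral t distribution with 127 degrees of freedom and noncentrality δ x sqrt(128). The article gives no value for δ, so a range is shown.

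| Natural fall (SD), assumed | P(significant fall), no service effect |
|---|---|
| 0 | 2.5% |
| 0.10 | 20% |
| 0.15 | 39% |
| 0.20 | 61% |
| 0.25 | 80% |
| 0.30 | 92% |
| 0.40 | 99% |
| 0.50 | over 99.9% |

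The planning r = 0.5 is stated for baseline and follow-up. Using it for baseline to discharge is a further assumption.

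**4. Which outcomes are affected.**

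| Table 1 effectiveness criterion | Comparator in the article |
|---|---|
| SIDAS ideation (primary) | none |
| Attempts and self-harm (survey) | none |
| ED (re-)presentation trends | historical, 2012–2021 |

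The point applies to the first two rows and not to the third.

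**The case against.** The strongest reply is that the design is openly non-randomized, that effectiveness is judged from several sources, and that the Abstract's conclusion refers to all of them. Table 1 does have a second effectiveness criterion based on surveillance trends, and the analysis plan considers cohort trends, COVID-19 and other confounders for it. The Economic evaluation section acknowledges missing information on service use without aftercare and plans to explore comparators. The dynamic modelling section plans sensitivity analyses on direct effects. All of that stands. It does not reach the primary outcome, where the criterion is fixed as a significant fall and no comparator is named. Disclosing the design does not make the change attributable.

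Several stronger readings are tempting and are not supported.
- *Natural recovery will produce a positive result.* No untreated SIDAS course is given. The Background says attempt risk is greatest just after discharge but stays high for up to 12 months, which covers discharge and follow-up. That concerns attempt risk rather than ideation scores, but it does not establish a rapid fall.
- *Regression to the mean alone equals the planned effect.* One could argue that entering 1 SD too high with r = 0.5 implies a fall of (1 − 0.5) x 1 = 0.5 SD. This is only an illustration: entry is by ED presentation and not by SIDAS score, and r is a planning correlation.
- *Self-harm and attempts can only fall from 100%.* Ideation-only entrants may have had no such event, and frequency and severity can rise in anyone. The 72-hour figure concerns the clinical assessment, counted from referral; no interval from event to survey is fixed.
- *Uncontrolled changes are the models' treatment effect.* No section says so.

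**Conclusion.** The point holds as a fault in the decision rule and in the conclusion drawn from it. As written, a significant fall in ideation, self-harm or attempts counts as effectiveness although these outcomes have no comparator and their baseline window normally contains the qualifying crisis. An inert service can pass. How often depends on an untreated fall that the article does not give: under the stated assumptions (128 completers, r = 0.5, two-sided 5% test) the chance is 2.5% with no natural fall, 61% at 0.2 SD, and 80% or more from 0.25 SD upward. The ceiling at baseline applies only to the binary past-month indicator, in participants who entered after an attempt or self-harm and were surveyed within a month of it. The ED re-presentation criterion is outside this point.

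**What to change.** 1. In the primary objective (Study aims), Table 1 and the Abstract, replace the significance criterion for survey outcomes with estimation of the change in service users, with a 95% CI. State that this change alone will not be attributed to the service. Base comparative statements on effectiveness on the Self-Harm Monitoring System analysis, with its limits as a historical comparison.
2. For self-harm and attempts, do not use the baseline-to-discharge test as evidence of effect; report occurrence after intake. Leave the YRBS items unchanged and add a separate question on whether the reported event was the episode that led to referral.
3. In the economic and system-dynamics models, wherever an uncontrolled survey change serves as an effect input, label it as uncontrolled and include a zero-effect scenario in the sensitivity analyses.

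The cost is a more modest claim, a registry update and one added survey question; baselines collected before the change, if any, will lack that item. These changes do not create a comparator for the primary outcome; they keep the conclusion within what the data can support. While the text is open, the sample-size statement should also be reconciled with the single-group analysis, since 184 fits a two-group formula.
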